##### Day after muscle biopsy and ultrasound (t_0_)

Start of enteral feeding at 6:00 am is independent of the study group.

##### Days 1–7 of observation (t_0_–t_6_)

Laboratory parameters and SOFA score will be analysed daily.

##### Day 7 of observation (t_6_)

Muscle biopsy and ultrasound of the quadriceps muscle will be repeated. A closeout visit will be performed.

#### Sample size

Power analysis and sample size estimation were performed a priori using G*Power 3.1. We assumed a final 2-way repeated measures analysis of variance (ANOVA) and set a sample size to ensure at least 90% power (1 − *β* = 0.9) at a significance level of 1% (*α* = 0.01).

The effect size was estimated according to our feeding previous protocols (Tables 1 and 2): the average administered protein was 1.6 g protein/kg BW/24 h at 34 h in the experimental group and 1.3 g protein/kg BW/24 h at 36 h in the control group. The estimation of the mentioned daily protein targets in this study was based on a preceding prospective observational pilot feasibility study with a high-protein formula (manuscript currently under review). For practical reasons, the 2-h difference was deemed negligible. Protein targets have been chosen in accordance with the current guidelines for enteral nutrition [35–41]. For the time series analysis, a moderate correlation between consecutive time points (0.5, Hinkle et al. [42]) was assumed. The 20 time points were chosen according to the four scheduled measurements and calculation of applied amount of protein across each study day for a specified minimum follow-up of 5 days (see inclusion criteria).

Sixty patients are required to have a 90% chance of detecting an increase from 1.3 g protein/kg BW/24 h in the control group to 1.6 g protein/kg BW/24 h in the experimental group after 36 h.

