**Day 2**													
Protein dose^1^	0.4			0.4			0.4			0.4			
Flow rate^2^	200–360			200–360			200–360			200–360			
Total protein^3^	1.4			1.6			1.6			1.6			

*GRV* gastric residual volume

^1^[g/kgBW/30 min], 4 nutrition cycles/24 h: each with 30 min nutrition followed by a 4-h break and 30 min GRV measure, night time break of 4 h. Total time of feeding, 2 h; GRV measurements, 2 h; break, 20 h

^2^[ml Fresubin© Intensive/30 min], depending on bodyweight

^3^Total of administered protein of the preceding 24 h [g/kgBW]

**Table 2 Tab2:** Continuous feeding protocol (control group)

Time	06:00–11:00	11:00–12:00	12:00–17:00	17:00–18:00	18:00–23:00	23:00–00:00	00:00–05:00	05:00–06:00
	Nutrition	Break + GRV	Nutrition	Break + GRV	Nutrition	Break + GRV	Nutrition	Break + GRV

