### Data collection and management

#### Plans for assessment and collection of outcomes

##### Assessment of primary outcome measure

The actual amount of protein intake within the last 24 h after every completed feeding administration cycle will be assessed. The actual amount of protein intake will be calculated according to the volume of the formula administered minus half of the recorded GRV. The decision to subtract half of GRV takes account of the fact that the recorded GRV will always consist of a mixture of nutrition formula and gastric juice. Results will be documented by the nurse responsible for the patient on a study-specific document and transferred to the eCRF, which will be accessible only to members of the study team. Assessment of primary and secondary outcome measures is outlined in Table 3.

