#### Adverse event reporting and harms

Since the utilised enteral nutrition is the standard formula for the initial phase in ICU patients at the University Hospital Basel, no severe adverse events relating to the components of this formula are expected after careful enrolment following the specified exclusion criteria. All study patients will be monitored with respect to any possible adverse events related to the administration of enteral nutrition. An accountability log for the nutrition formula will be provided for each patient with the batch number of the administered bags.

Fresubin© Intensive comes under risk category A in our trial. It is a medicinal product authorised in Switzerland, and its use in this study is in accordance with the prescribing information: critically ill ICU patients with increased need for protein. Possible side effects of intermittent feeding in the intervention group are expected to be similar to the familiar side effects (e.g. meteorism, diarrhoea and constipation) of continuous feeding. The aspiration risk will be limited due to frequent controls of GRV after every feeding cycle. The enteral feeding will be stopped immediately in case any adverse events, including GRV > 300 ml, vomiting, regurgitation or aspiration, occur. Feeding will be restarted at the next planned cycle at the highest dose previously tolerated. If a patient of the experimental group does not tolerate the administered dose of nutrition over three consecutive feeding cycles (despite common prokinetics as 100 mg erythromycin and 10 mg metoclopramide, whenever no contraindication is applicable), he or she will be crossed-over to the standard continuous feeding group. If a patient of the CF group does not tolerate the administered dose of nutrition over three consecutive cycles, the treating physician will discuss how to proceed together with the study team.

For monitoring of hypo/hyperglycaemia, we will determine the blood glucose with an interval of 3 h maximum and if applicable administer insulin according to our standardised ICU protocol considering the state of health and presence of diabetes mellitus.

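### The sample size uses scheduled 24-hour totals (1.6 and 1.3 g/kg) as if they were averages of delivered protein, so the 90% power describes the prescription

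*Protocol article*

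**What the plan says.** The Sample size section sets 90% power at a "significance level of 1"% for a two-way repeated measures ANOVA, with correlation 0.5 and 20 time points. On the effect it says: "The effect size was estimated according to our feeding previous protocols (Tables 1 and 2"). For the intermittent arm it reports that "the average administered protein was 1.6 g protein/kg BW/24 h at 34 h in the experimental group". The comparator figure, two hours later on the clock, is given as "1.3 g protein/kg BW/24 h at 36 h in the control group". The section's conclusion reads: "Sixty patients are required to have a 90% chance of detecting an increase", the increase being that between these two values. It gives no SD, no standardised effect size and no G*Power test family. A pilot feasibility study is cited as the basis for the daily protein targets, but no delivered mean or SD from it is shown.

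The footnote to Tables 1 and 2 defines their running total as "Total of administered protein of the preceding 24 h [g/kgBW"]. The measured outcome differs. Under Assessment of primary outcome measure, intake is "calculated according to the volume of the formula administered minus half of the recorded GRV". Under Adverse event reporting and harms, "The enteral feeding will be stopped immediately in case any adverse events, including GRV > 300 ml, vomiting, regurgitation or aspiration, occur". Feeding then resumes at the next cycle, at the largest dose the patient has already tolerated. Intermittent-arm patients who fail three cycles in a row move to continuous feeding.

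**The concern.** The two values are presented as averages of protein given, yet they coincide with what the schedules prescribe if every feed is delivered in full and nothing is deducted. Measured intake cannot exceed that and will often be less. The difference of 0.3 g/kg is the only effect that the section states, so the 90% figure rests on it. If it is a property of the prescription, the power claim does not carry over to the delivered protein that will be compared. The means and any usable SD also cannot both be true.

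**Working it through.** **1. Where 1.6 and 1.3 come from.** Doses per cycle (g/kg), from Tables 1 and 2:
- Intermittent (IF): 0.1, 0.2, 0.4, 0.4, then 0.4 each. Sum of the last four at cycle 6: 0.4 + 0.4 + 0.4 + 0.4 = **1.6**.
- Continuous (CF): 0.05, 0.1, 0.2, 0.3, then 0.4 each. Sum of the last four at cycle 6: 0.2 + 0.3 + 0.4 + 0.4 = **1.3**.

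With a 06:00 start, IF cycle 6 closes with its GRV check at about 34 h and CF cycle 6 closes at 36 h. Values and times both match the Sample size section. The CF figure is the ceiling at 36 h only; its schedule reaches 1.6 at the end of day 2.

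**2. Ceiling and SD.** For an outcome between 0 and a ceiling c, with mean m, the variance is at most m(c − m). At m = c this is zero.

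**3. What N = 60 would need.** The plan's 60 cannot be computed forward because no SD or f is stated. Solving backwards from 30 per arm, alpha 0.01, 90% power and a gap of 0.3:
- Two-sample t test at one time point: d = 1.026, so SD = 0.3/1.026 = 0.29.
- Between-group effect over 20 points with correlation 0.5: variance factor (1 + 19 × 0.5)/20 = 0.525, so SD = 0.29/√0.525 = 0.40.

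Setting SD² = m(c − m) and taking the larger root gives the highest possible mean:

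| SD | IF mean at most | CF mean at most |
|---|---|---|
| 0.29 | 1.54 | 1.23 |
| 0.40 | 1.49 | 1.16 |

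These SDs are illustrations. Another test family would imply a different one, but any SD above zero rules out means of 1.6 and 1.3.

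**4. GRV deduction alone** (assumed 70 kg, 50 ml per cycle; formula 0.1 g protein/ml). Loss = 4 × 25 ml × 0.1 / 70 = 0.143 g/kg. IF becomes 1.457 and CF 1.157; the gap stays 0.30.

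**5. Stopped feeds.** All outcomes of six cycles were enumerated. Assumptions: stops are independent with a constant rate; a stopped cycle is lost in full; the next cycle uses the largest dose already tolerated (the first dose if none), then the ramp resumes; no GRV deduction and no crossover. SD is the root mean of the two arm variances. Power is a two-sided t test with 30 per arm, alpha 0.01, 58 df, noncentrality (gap/SD) × √15. The documents give no stop rates.

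| Stop rate IF / CF | IF mean | CF mean | Gap | SD | Power |
|---|---|---|---|---|---|
| 0 / 0 | 1.60 | 1.30 | 0.30 | 0 | not defined |
| 5% / 5% | 1.47 | 1.15 | 0.33 | 0.26 | 99% |
| 10% / 10% | 1.35 | 1.01 | 0.34 | 0.34 | 88% |
| 20% / 20% | 1.10 | 0.76 | 0.34 | 0.41 | 70% |
| 10% / 5% | 1.35 | 1.15 | 0.20 | 0.30 | 46% |
| 20% / 10% | 1.10 | 1.01 | 0.09 | 0.39 | 4% |
| 5% / 10% | 1.47 | 1.01 | 0.47 | 0.30 | over 99% |

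No arm with stops reaches its ceiling. The gap moves in both directions.

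**The case against.** The strongest reply is that power depends on the difference, and lower arm means do not imply a smaller one. That stands. Equal absolute losses cancel, and equal stop rates widen the gap a little because the continuous arm is still ramping up. The protocol's own rationale (Strengths and limitations; Ethical justification) expects fewer interruptions with intermittent feeding and missed targets with continuous feeding, which would make 0.3 conservative. The restart rule also costs nothing in dose once a 0.4 feed has been tolerated. A reader might therefore infer from the ceiling argument that 90% is overstated, that 0.3 is out of reach or that 60 is too few. The documents support none of these: the direction depends on which arm loses more, and without an SD, 60 is neither confirmed nor refuted.

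A second reply is that the values may be pilot averages that happen to equal the schedule. The pilot cannot be seen, but the section attributes the effect size to Tables 1 and 2, mentions the pilot for the targets, and matches the schedule to one decimal in both arms. Rounding does not help much. A mean of 1.55 would print as 1.6, but at 70 kg a shortfall of 0.05 g/kg allows only 70 ml of GRV in total over four cycles (0.05 × 70 / 0.1 = 35 ml deducted) and no stopped feed. Its largest possible SD, √(1.55 × 0.05) = 0.28, is still below 0.29.

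Third, a condensed article may leave the SD to the full protocol. That is accepted, so the missing SD is not the point in itself. The point is that the means which are stated are scheduled values described as averages.

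**Conclusion.** The concern holds as a fault in the effect-size input. The 1.6 and 1.3 are each arm's scheduled ceiling at cycle 6, they cannot be the means of delivered protein with any spread, and the 90% power therefore belongs to the prescription. This rests only on the tables, the outcome definition and the stopping rules; it does not depend on the back-solved SDs.

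The size and direction of the effect on power are open. In the illustrations the gap runs from 0.09 to 0.47 and the single-time-point power from 4% to over 99%. Those figures rest on assumed stop rates and a simple t test, not the planned ANOVA, and show sensitivity only. The correction should be made, because the sizing is the trial's stated justification for 60 patients.

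**What to change.** In the Sample size section:
1. Label 1.6 and 1.3 as scheduled trailing 24-hour totals.
2. In the calculation, replace them with the mean and SD of delivered protein (volume given less half of GRV) per regimen at about 36 h, taken from the cited pilot. Intermittent-arm patients who are stopped or crossed over count in the intermittent arm. If the pilot covers one regimen only, state an assumed delivered fraction for each arm.
3. State the SD and the test family used.
4. Restate the power of 60 patients in a short table with equal loss, heavier loss in the intermittent arm and heavier loss in the continuous arm.

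The cost is a recalculation, revised text and possibly a less favourable power figure. It needs no added patients and no change to any feeding rule.

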##### Primary and secondary analysis

A 2-way repeated measures ANOVA with post hoc pairwise comparison using a Bonferroni correction will be used to test for differences in protein administration at each time point for the control and experimental groups. The same method will be used to test differences in all secondary outcomes between groups. Additional statistical modelling using generalised linear models will be performed to inspect relationships between baseline patient characteristics, and primary and secondary outcomes.

All analyses on primary and secondary endpoints will be calculated by the study team in close collaboration with the Clinical Trial Unit of the University Hospital Basel.

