### Sample size

Sample size was estimated to prove the superiority of IF compared to CF regarding the time (in hours) to reach the protein target of 1.5 g protein/kg BW/24 h.

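### The 90% power stated for 60 patients does not belong to the test it is claimed for: the sizing takes one 36-h gap of 0.3 g/kg, ignores the Bonferroni correction, and is not for time to target

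*Protocol article*

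**What the plan says.** Sample size (Methods) describes an a priori G*Power calculation for a two-way repeated-measures ANOVA, "set a sample size to ensure at least 90% power", with alpha 0.01 and a correlation of 0.5 between consecutive time points. The effect is read from the feeding schedules: "1.6 g protein/kg BW/24 h at 34 h in the experimental group and 1.3 g protein/kg BW/24 h at 36 h in the control group". This two-hour offset is treated as negligible. On the number of points: "The 20 time points were chosen according to the four scheduled measurements and calculation of applied amount of protein across each study day", over a minimum follow-up of five days. The conclusion is: "Sixty patients are required to have a 90% chance of detecting an increase from 1.3 g protein/kg BW/24 h in the control group". Its counterpart for intermittent feeding is 1.6 g/kg, and both amounts refer to 36 h.

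No SD and no f is given, and the section does not say whether the group main effect or the group-by-time interaction was powered.

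Primary and secondary analysis plans the two-way ANOVA with "post hoc pairwise comparison using a Bonferroni correction" to compare the arms at each time point. Primary outcome measure defines the primary outcome as hours from first study feeding to the target of at least 1.5 g/kg/24 h. Sample size (Discussion) says: "Sample size was estimated to prove the superiority of IF compared to CF regarding the time (in hours") to reach that target.

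**The concern.** Three different things carry the same 90%: a difference in amount at one time (the effect used), a 20-point ANOVA (the model used) and the time to target (the outcome named in the Discussion). They have different power.

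- A gap at one time is not the group effect averaged over 20 points when the schedules converge on day 2.
- The comparison that does look at the 36-h gap is corrected for multiplicity, while the sizing sets alpha at 0.01 and mentions no correction.
- No calculation is shown for time to target.

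At stake is how a null result would be read. If the 36-h comparison or the time to target shows no difference, readers will take it as evidence from a trial with 90% power for that question, and the article does not establish this.

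**Working it through.** **Inputs.** Alpha 0.01, power 0.90, m = 20 points, correlation ρ = 0.5 and N = 60 are from Sample size (Methods). The 30 per arm is from Data management. The doses are from Tables 1 and 2. Sidedness is not stated; F tests and two-sided t tests are used here.

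**Step 1: the stated 60.** It cannot be reproduced without an SD or f, so N = 60 is solved backwards.

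- Between-groups option: λ = f²·N·m/[1+(m−1)ρ], df 1 and 58. Power 0.90 needs f = 0.372. With f = 0.15/SD for a 0.3 gap, SD = 0.15/0.372 = 0.40.
- Single 36-h t test: power 0.90 needs d = 1.026, so SD = 0.3/1.026 = 0.29.
- Interaction option: λ = f²·N·m/(1−ρ), df 19 and 1102. Power 0.90 needs f = 0.119. If f = 0.15/SD, then SD = 1.26, nearly as large as the intake itself. This reading is not relied on below.

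**Step 2: the scheduled gap.** Rolling 24-h totals (g/kg) by cycle:

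| Cycle | 1 | 2 | 3 | 4 | 5 | 6 | 7 | 8 to 20 |
|---|---|---|---|---|---|---|---|---|
| Intermittent | 0.10 | 0.30 | 0.70 | 1.10 | 1.40 | 1.60 | 1.60 | 1.60 |
| Continuous | 0.05 | 0.15 | 0.35 | 0.65 | 1.00 | 1.30 | 1.50 | 1.60 |
| Gap | 0.05 | 0.15 | 0.35 | 0.45 | 0.40 | 0.30 | 0.10 | 0 |

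The 0.3 used for sizing is the sixth-cycle gap. The gaps sum to 1.8, so the mean over 20 points is 1.8/20 = 0.09. This assumes full delivery and 1.6 in both arms after day 2.

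**Step 3: power with 30 per arm.**

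- 36-h comparison: noncentrality = (0.3/SD)·√15, 58 df. The corrected level is taken as 0.01/20 = 0.0005, or 0.05/20 = 0.0025 if the family level is 0.05.
- Group main effect: f = 0.045/SD in the between-groups formula.
- Interaction: the squared gaps sum to 0.61, and 0.61 − 20·0.09² = 0.448. So f = √(0.448/80)/SD = 0.0748/SD. This gives λ = 82 at SD 0.40 and 157 at SD 0.29, with sphericity assumed.

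| Test | SD 0.40 | SD 0.29 |
|---|---|---|
| 36 h, alpha 0.01, uncorrected | 59% | 90% |
| 36 h, 0.01/20 | 23% | 61% |
| 36 h, 0.05/20 | 40% | 79% |
| Group main effect, mean gap 0.09, ρ = 0.5 for all pairs | 8% | 16% |
| Group main effect, correlation 0.5 decaying with lag (AR(1)) | 37% | 70% |
| Group-by-time interaction, alpha 0.01 | over 99% | over 99% |

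**Step 4: the Discussion.** Sample size (Methods) compares two amounts at a fixed time. It contains no distribution of times, event rate or hazard ratio. The statement in the Discussion that the size was estimated for time in hours therefore has no calculation behind it in this document.

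**The case against.** The strongest reply is that the missing SD makes every power figure conditional. That stands. A reader might infer that the 90% fails under every assumption, and the document does not support this. With SD 0.23 the corrected 36-h comparison still has 90% at 0.01/20, and with SD 0.12 the group main effect does too. However, at SD 0.23 an uncorrected 36-h test at alpha 0.01 would need only about 40 patients, so sixty would not then be what is required for it.

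A reader might also infer that the whole planned ANOVA is underpowered. It is not. The interaction depends on how the gap changes over time, not on its mean, and has at least 90% power up to SD 0.63. But the article's claim is about the 36-h gap, and an interaction does not say which arm is ahead or when.

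The 8% and 16% depend on applying 0.5 to all pairs of points. The article speaks of consecutive points, and with decay over lag the figures rise to 37% and 70%.

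It is tempting to add that rolling four-cycle totals must correlate at 0.75 or more with their neighbours. That is no bound. During ramp-up the totals are partial sums: with independent cycles of equal variance the first adjacent correlation is 0.71, and with cycle SD proportional to dose it is 0.45.

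It is fair, too, that the comparisons are called post hoc, that a family of 20 is an inference, and that actual intake will differ from the schedule. A condensed article may leave detail to the analysis plan. Even so, this article attaches its 90% explicitly to the 36-h gap and, in the Discussion, to time to target.

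**Conclusion.** Wrong as written, in a limited sense: the stated 90% does not match the test it is claimed for. At the SDs implied by N = 60 (0.40 or 0.29), the corrected 36-h comparison has 23% or 61% power at 0.01/20, and 40% or 79% at 0.05/20. The group main effect has 8% or 16% under a common correlation of 0.5, and more if correlation decays. These figures assume full delivery of the schedule, equal SD at all points and 20 comparisons in the Bonferroni family. Two parts need no SD: the sizing makes no allowance for the planned correction, and the Discussion attributes to time to target a calculation made on an amount of protein. It is not shown that 60 patients are too few.

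**What to change.** Keep 60 patients, and name one pre-specified test to which the power refers. State the pilot SD (or, for time to target, the assumed effect), and restate the power for that test.

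- Time to target needs no change to the declared primary outcome. Setting 4(z₁+z₂)²/(ln HR)² = 60 events, with z₁+z₂ = 2.576 + 1.282 = 3.858 for two-sided alpha 0.01, gives ln HR = 2·3.858/√60 = 0.996. The detectable hazard ratio is about 2.7. This assumes proportional hazards and that all 60 patients reach the target; with fewer events the detectable ratio is larger.
- A single 36-h comparison must be declared primary and taken out of the Bonferroni family. At two-sided alpha 0.01 with 30 per arm and a gap of 0.3, power is 88%, 60% and 38% at SD 0.3, 0.4 and 0.5.

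If a repeated-measures power statement is kept, it should give f, name the ANOVA effect and use the gap profile of Tables 1 and 2. Sample size (Discussion) should then be reworded to agree with whichever test is chosen.

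The cost is rewording two sections. No extra patients are needed, but the stated power may become less favourable.

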#### Recruitment

The ICU study team will screen every patient with an expected need for enteral nutrition for a minimum of 5 days and a predicted ICU stay of at least 5 days within the first 48 h after ICU admission for study eligibility.

### Assignment of interventions: allocation

#### Sequence generation

Trial staff will have access 24/7 to the electronic case report form (eCRF) where patients are screened and randomised to one of the trial arms. Randomisation will be performed using electronic case report form (REDCap) (see the “Data management” section). A randomisation list will be established using computer-generated random numbers. We will use block randomisation, and patients will be stratified for neurotrauma.

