## Strengths and limitations of this study

The study’s main strength is the implementation of an advanced and promising therapy for an unsolved problem: rapid muscle wasting in critically ill patients. The short intermittent feeding times in the experimental group (a total of 2 h feeding time and total break time of 22 h) may allow more flexible patient care compared to the continuous control group (a total of 20 h feeding time and total break time of 4 h).If the short intermittent feeding times are well tolerated, patients in the experimental group are expected to reach the daily protein target faster, as there are fewer feeding interruptions.Until today, there is no known study that directly measures muscle atrophy by ultrasound and biopsy in relation to differing feeding protocols in critically ill patients. Due to the quantitative measurement of the quadriceps muscle by ultrasound and histological evaluation of biopsies, the study could provide new reliable data in the field of muscle wasting in critically ill patients and a direct comparison of the two feeding regimens.The study is limited by the wide heterogeneity of type and severity of underlying disease of intensive care unit (ICU) patients included in the study. These variable conditions will be addressed according to assessment and analysis of the Simplified Acute Physiology Score II (SAPS II) score.

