#### Methods for additional analyses (e.g. subgroup analyses)

We stratified for patients suffering from neurotrauma, which will represent a subgroup for analysis.

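### Randomisation is stratified by neurotrauma, but the stated group-by-time ANOVA has no stratum term and SAPS II has no stated place in the treatment comparison; the likely cost is a conservative test and some forgone power

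*Protocol article*

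**What the plan says.** All references are to the protocol article.

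- *Sequence generation*: "We will use block randomisation, and patients will be stratified for neurotrauma".
- *Primary and secondary analysis*, on the group comparison: "A 2-way repeated measures ANOVA with post hoc pairwise comparison using a Bonferroni correction will be used to test for differences in protein administration". Groups are compared at every time point, and the same method is then extended to all secondary outcomes.
- *Sample size*: the trial is sized on that model. "We assumed a final 2-way repeated measures analysis of variance (ANOVA"), with alpha 0.01, power 90%, 20 time points and correlation 0.5.
- *Methods for additional analyses*: "We stratified for patients suffering from neurotrauma, which will represent a subgroup for analysis". This is the only role given to neurotrauma in the analysis.
- *Strengths and limitations of this study*: after naming the varied type and severity of disease as the limitation, the article says "These variable conditions will be addressed according to assessment and analysis of the Simplified Acute Physiology Score II (SAPS II) score".
- *Secondary outcome measures*: SAPS II is listed as a baseline assessment, together with APACHE II and NUTRIC.
- *Primary and secondary analysis*, on further modelling: "Additional statistical modelling using generalised linear models will be performed to inspect relationships between baseline patient characteristics, and primary and secondary outcomes". Neither SAPS II nor neurotrauma is named there, and the text does not say whether treatment group is in these models.

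**The concern.** Stratified blocks force the two arms to be similar in their share of neurotrauma patients. That removes the between-stratum difference from the true sampling variation of the treatment contrast. An analysis without the stratum still counts that difference as residual variation between patients, so its standard error is too large whenever neurotrauma is related to the outcome. Part of the precision obtained by stratifying is then lost.

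SAPS II raises a related but separate matter. The article presents it as the way heterogeneity will be handled, yet no stated treatment comparison contains it. Read literally, the analysis section would apply the between-group method to SAPS II itself, because it is listed as a secondary outcome. A test of a baseline score between randomised arms does nothing about heterogeneity.

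At stake is precision in a trial of 60 mixed ICU patients tested at the 1% level.

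**Working it through.** **The plan's own figure.** The stated 60 patients can be neither confirmed nor refuted, because no SD or effect size is given. Solving backwards for 90% power at alpha 0.01 with a difference of 1.6 − 1.3 = 0.3 g/kg BW/24 h:

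- The between-groups F test (20 time points, correlation 0.5) needs f of about 0.37, so d = 2f of about 0.74 and SD of about 0.3/0.743 = 0.40.
- A simple two-group comparison at 36 h needs SD of about 0.30.

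Neither back-calculation uses the stratum or SAPS II, so the stated 90% does not rely on adjustment.

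**Inputs for the check.**

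- From the article: 60 patients, 30 per group, alpha 0.01.
- Assumed: two-sided test, blocks of 4, neurotrauma share 15%, 30% or 50%, and stratum R² (share of between-patient outcome variance explained by neurotrauma) from 0 to 0.30.
- The effect is set at d = 1.026 total SD, which gives the unadjusted two-group test 90% power at 60 patients.

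**Approximation.** With the stratum balanced, the true variance of the group contrast is proportional to 1 − R², while the unadjusted analysis estimates it as if proportional to 1. The critical value on 58 degrees of freedom is 2.663, so the effective cut-off is 2.663/√(1 − R²):

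- R² = 0.05: 2.663/0.975 = 2.732, type I error 0.0083
- R² = 0.10: 2.663/0.949 = 2.807, type I error 0.0068
- R² = 0.20: 2.663/0.894 = 2.978, type I error 0.0042
- R² = 0.30: 2.663/0.837 = 3.183, type I error 0.0023

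**Simulation.** Stratified blocks, 6,000 null trials and 4,000 power trials per setting; ranges are over the three shares. The Monte Carlo standard error of the type I error is about 0.0013.

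| Stratum R² | Type I error, stratum omitted | Power, stratum omitted | Power, stratum included |
|---|---|---|---|
| 0 | 0.010–0.013 | about 90% | about 90% |
| 0.05 | 0.008–0.012 | 90–91% | 91–92% |
| 0.10 | 0.006–0.009 | 90–91% | 92–93% |
| 0.20 | about 0.004 | 92% | 96% |
| 0.30 | 0.001–0.003 | 93–94% | 98% |

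With the stratum included, type I error stays near 0.01 (0.008–0.015). The simulation and the approximation agree.

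**SAPS II.** With a SAPS II-like covariate at a 30% neurotrauma share:

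- Covariate R² 0.10, stratum R² 0.10: power 91% unadjusted, 93% with the stratum, 95% with both.
- Covariate R² 0.20, stratum R² 0.05: power 90%, 91% and 97%.

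SAPS II is not a stratification factor, so its imbalance between arms is left to chance and the unadjusted test already allows for that. Leaving it out loses precision but does not disturb the type I error.

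**Scope.** These figures describe between-patient group contrasts. A stratum effect that is constant over time drops out of the group-by-time error term, so that part of the ANOVA is not affected.

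**The case against.** The strongest reply is that the article defers detailed methodology to a statistical analysis plan that is not shown, and that covariates and stratum terms commonly go there. Nothing says the stratum will be excluded. This would settle the matter if the article were silent, but it names the model and its number of factors, and sizes the trial on the same model. Its section on communicating amendments says that substantial departures from the outlined analysis require an amendment. The outline is therefore meant to bind, and as written it has no stratum term.

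On SAPS II, the limitation paragraph does not promise an adjusted treatment comparison, and the generalised linear models on baseline characteristics may be what is meant. That reading is possible. The point that stands is narrower: no stated treatment comparison contains SAPS II, so the reader cannot tell how it addresses heterogeneity.

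Three further objections are right and limit the point. Protein delivery follows a fixed per-kilogram schedule, and the article does not say that neurotrauma predicts it, so the effect may be nil. The neurotrauma subgroup was never offered as a substitute for adjustment. And forgone power is not a shortfall, because the design was sized without adjustment.

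A reader might infer that the p-values are unsafe in the sense of too many false positives. The documents and the arithmetic do not support this: the error is on the conservative side and comes from the stratum alone.

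**Conclusion.** The mismatch between stratified allocation and an analysis without the stratum is in the text and is worth correcting. Its consequence is conditional and modest. If neurotrauma explains 5% or less of outcome variance, type I error remains about 0.01 and at most about 1 point of power is forgone. At 10% the figures are 0.006–0.009 and about 2 points, and at 20–30% they are about 0.004 falling to 0.001–0.003, with 4–5 points forgone. If neurotrauma is not prognostic, there is no effect.

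These sizes rest on the assumed share, block size and prognostic strength, none of which the article gives, and they apply to between-patient contrasts. Omitting SAPS II is a matter of precision only. It would be wrong to conclude that the trial misses its 90% power for this reason, since nothing in the article shows that. Confidence is high on what the text says and low on how large the effect is in this trial.

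**What to change.** Add one sentence to *Primary and secondary analysis*: the between-group models for the primary outcome and for the post-baseline secondary outcomes include the randomisation stratum (neurotrauma) and baseline SAPS II (continuous) as prespecified terms.

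Two consequential edits follow:

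- Treat the baseline scores under *Secondary outcome measures* (APACHE II, SAPS II, NUTRIC) as descriptive. SAPS II cannot be both a covariate and an outcome in the same comparison.
- If the primary outcome is analysed as time to target, stratify that analysis by neurotrauma.

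If the sponsor prefers not to adjust for SAPS II, the limitation paragraph should say that the score is used only descriptively or in the exploratory models.

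The cost is one sentence and one or two degrees of freedom of the 60 − 2 = 58 available between patients. SAPS II is already collected at baseline, and neurotrauma status must be known to randomise. If neither term proved prognostic, the simulated loss from including both was under 1 point of power (for example 89.7% to 88.8% at a 30% share).
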